### Sample size/power calculation

Based on former international studies [25] with an average DUI of 19 months and an effect size of 0.4, we considered a DUI reduction of 4.8 months or 25% as clinically relevant. Thus, for a two-sided type-I error of 5% two samples with 100 participants each are needed to reach statistically significance with a power of 80%.

### Primary outcome

The primary outcome is the DUI, defined as the time in months between the onset of AN and first specific treatment.

### Secondary outcome

As secondary outcome, DUC, current ED pathology as well as comorbid depressive or anxious psychopathology are assessed. Depression and anxiety are the most frequent comorbid psychiatric disorders accompanying AN (e.g. [5,6]).

### Study hypotheses

It is hypothesized that the systemic intervention of *psychenet* decreases the DUI in the post-group compared to the pre-group. As described above it is of great relevance to detect and treat individuals with AN sooner. Next to individual factors such as age [27] there are systemic aspects like sufficient information, availability and networking of different components of the health care system influencing patient flow into ED-specific care. The intervention focuses on spreading information about EDs, informing about paths to treatment, improving the networking of different healthcare professionals and extending the offer by establishing a special outpatient clinic. Therefore, it seems reasonable to assume that the systemic intervention decreases the duration until an ED-specific treatment is initiated. For the same reasons it is hypothesized that the systemic intervention decreases the DUC. Moreover, it is assumed that the systemic intervention leads to a reduced ED pathology as well as a reduced comorbidity with depression and anxiety at the beginning of treatment. It is further suspected that this effect is mediated by the DUI. An earlier intervention and a shorter duration of illness prior to treatment initiation may lead to a reduced severity of AN and a reduced comorbidity because treatment starts before a chronification can occur. Therefore, it is conceivable that the expected shorter DUI in the post-group leads to a decreased ED pathology and comorbidity at treatment initiation. Due to the lack of previous research these hypotheses will be analyzed exploratorily.

To display them at a glance, the hypotheses of the study are:The systemic intervention decreases the DUI in the post-group compared to the pre-group.The systemic intervention decreases the DUC in the post-group compared to the pre-group.The systemic intervention decreases the ED pathology at treatment initiation in the post-group compared to the pre-group via DUI.The systemic intervention decreases the comorbidity with depression and anxiety at treatment initiation in the post-group compared to the pre-group via DUI.

Figure 2 illustrates the expected impact of the systemic intervention on the primary and secondary outcome parameters.

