## Methods

### Study design

For the study purpose, a pre-post between-subject design was chosen. DUI, duration until first contact (DUC), current ED pathology and comorbidity are measured before and after the implementation of the systemic intervention. The pre-data collection takes place between November 2012 and May 2013. Twelve months are planned for the systemic intervention. The post-data collection takes place between May 2014 and November 2014. Figure 1 illustrates the course of the data collection.

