### Study procedures

#### Inclusion and exclusion criteria

In order to participate in the study, a signed informed consent is necessary. Patients below 16 years are required to provide additional informed consent from a parent or legal guardian. Moreover, participants need to have female sex, should be a minimum of ten years old and have a treatment diagnosis of typical or atypical (one criterion absent) AN according to the DSM-IV [33]. Furthermore participants should currently receive their first ED-specific in- or outpatient treatment or be current client of an ED-specific counselling center. Exclusion criteria are insufficient knowledge of the German language as well as substantial organic or psychological complaints preventing participation from the recruiting practitioner’s point of view.

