#### Recruitment

The recruitment is coordinated in cooperation with different ED-specific treatment settings in Hamburg and adjacent areas, i.e. inpatient wards, day clinics, outpatient departments and ED-specific counselling centers. Included institutions offer evidence-based treatment for AN based on the German S3-Guidelines for EDs [34]. A total of eleven clinics, nineteen outpatient departments and four counselling centers are asked to support the project with recruiting participants. A special network meeting is used to inform cooperating practitioners about the study’s content, procedure, and recruitment as well as to provide practitioners with study materials (e.g. written information about the course of recruitment, study design, inclusion and exclusion criteria as well as informed consent forms and questionnaires for participants). During the study, cooperating practitioners regularly receive phone calls to settle any questions and promote adherence.

Cooperating practitioners select eligible participants in line with inclusion and exclusion criteria. Participants found eligible are verbally informed about the aims and procedure of the study and are additionally provided with written material. In case of willingness to participate, participants are asked to sign the informed consent. Practitioners then hand out the questionnaire set, which is described later in this paper. All cooperating practitioners are required to return the completed questionnaires as well as the signed informed consents to the research team. Once all documents are complete, participants are contacted for a structured telephone interview.

The procedure will be identical in the post-survey. Participants who participated in the pre-survey are excluded from participation in the post-survey. Between the two points of data collection the systemic intervention takes place.

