#### ED pathology

ED pathology is measured by the BMI in combination with the German version of the *Eating Disorder Examination Questionnaire EDE*-*Q* [36]. The BMI is calculated from body weight and height. Current weight is requested in the questionnaire as well as in the telephone interview. Additionally, weights at disorder onset, at treatment initiation as well as at point of lowest weight are assessed in the telephone interview. Given the community-based character of the present study, it is not feasible to get externally validated weight measurements for all participants. Additionally, since patients with AN in in- and outpatient treatment institutions are weighted weekly, self-reported weight will be considered adequate. The *EDE*-*Q* assesses specific ED psychopathology on four subscales, which are restraint, eating concern, weight concern, and shape concern. For patients below the age of sixteen, the child version *Ch*-*EDE*-*Q*, [37,38] is used. The psychometric criteria of the *EDE*-*Q* are satisfactory. Objectivity is given and the test is very reliable with an intern consistency of α = .97 and a retest-reliability of r = .88. Validity could be confirmed as well [36].

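### Exploratory hypotheses 3 and 4 are about severity at treatment initiation, but the scores are taken during first treatment with no stated time window or adjustment for time in treatment

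*Protocol article*

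**What the plan says.** **The hypotheses.** The Study hypotheses section of the protocol article places both severity hypotheses at the start of treatment. Hypothesis 3: "The systemic intervention decreases the ED pathology at treatment initiation in the post-group compared to the pre-group via DUI". Hypothesis 4: "The systemic intervention decreases the comorbidity with depression and anxiety at treatment initiation in the post-group compared to the pre-group via DUI". The same section says that they are to be analysed in an exploratory way.

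**The outcome.** Study design: "DUI, duration until first contact (DUC), current ED pathology and comorbidity are measured before and after the implementation of the systemic intervention". Secondary outcome: "DUC, current ED pathology as well as comorbid depressive or anxious psychopathology are assessed". Neither section ties the severity measures to treatment start.

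**Who is measured, and when.** Inclusion and exclusion criteria: "Furthermore participants should currently receive their first ED-specific in- or outpatient treatment or be current client of an ED-specific counselling center". Recruitment has the treating practitioner select the patient and obtain consent; then "Practitioners then hand out the questionnaire set, which is described later in this paper". The telephone interview comes later, once the documents are complete. No section gives a maximum time from treatment start to questionnaire.

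**Weight.** Current weight is asked in both the questionnaire and the interview. The ED pathology section also says that "weights at disorder onset, at treatment initiation as well as at point of lowest weight are assessed in the telephone interview".

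**The model.** Statistical analyses names DUI and DUC as dependent variables. The predictors are assessment period, recruitment setting (random), age and contact with the intervention (both fixed). Time in treatment is not among them.

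**The concern.** DUI ends when treatment begins. The chain proposed for hypotheses 3 and 4 is that the intervention shortens DUI and a shorter DUI means less severe illness when treatment starts. A score taken some time into treatment contains that severity plus whatever has changed since. Only the first part bears on the hypotheses.

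Two things follow.

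- The EDE-Q, PHQ-9 and GAD-7 scores and current BMI do not measure what the hypotheses name, even if both samples have spent equally long in treatment.
- If the samples differ in time in treatment, the pre/post difference carries that gap as bias, and part of it may be credited to, or hidden from, the path through DUI.

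At stake is the reading of the secondary severity results: a difference could come from treatment stage, or a real difference could be masked by it.

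**Working it through.** **1. The time points side by side**

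| Element | Time point | Section |
|---|---|---|
| Hypotheses 3 and 4 | Treatment initiation | Study hypotheses |
| Listed outcome | Current, with comorbidity alongside | Study design; Secondary outcome |
| Patients | Already in first treatment or counselling | Inclusion and exclusion criteria |
| Questionnaire | After selection and consent, no window | Recruitment |
| Initiation value available | Weight only, by recall | ED pathology |

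ED pathology justifies self-reported weight by the weekly weighing of patients in treatment institutions, so participants are expected to be under treatment when measured. EDE-Q, PHQ-9 and GAD-7 have no counterpart at initiation.

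**2. The plan's own figure**

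Sample size/power calculation gives an effect size of 0.4, two-sided 5%, 80% power and 100 per group.

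- n = 2 × (1.96 + 0.842)² / 0.4² = 98.1, so 99 per group by the normal formula.
- The t-test version gives 99.08, so 100.

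The figure is reproduced, but it sizes DUI only. The article gives no effect size for the severity scores.

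**3. Size of the possible bias**

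Bias = (change in SD per month of treatment) × (difference in mean months in treatment). Both inputs are assumptions from outside the documents.

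| SD per month | 0.5 month | 1 month | 2 months |
|---|---|---|---|
| 0.05 | 0.025 | 0.05 | 0.10 |
| 0.1 | 0.05 | 0.10 | 0.20 |
| 0.2 | 0.10 | 0.20 | 0.40 |

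With 100 per group the standard error of a standardised difference is √(2/100) = 0.141. With no true effect, an unadjusted two-sided 5% test would reject in 5.4% of studies at a bias of 0.025, 10.9% at 0.10, 29.3% at 0.20 and 80.7% at 0.40.

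**4. Size of the effect sought**

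If DUI falls by 0.4 SD as planned, the mediated effect on a score is 0.4 × b, where b is the standardised slope of severity on DUI. For assumed b of 0.1, 0.2 and 0.3 this is 0.04, 0.08 and 0.12 SD. Most cells of the table are of that order or larger.

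**5. Does the plan itself create a gap in time in treatment?**

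Recruitment bars pre-survey participants from the post-survey. Pre-recruitment ends in May 2013 and post-recruitment starts in May 2014, so the bar reaches only patients still in first treatment after about 12 months. Assume exponential treatment lengths with mean m.

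- Share of current patients beyond 12 months: exp(−12/m) = 5%, 14% and 37% for m = 4, 6 and 12 months.
- Fall in mean elapsed time if all of them are barred: 12 / (exp(12/m) − 1) = 0.6, 1.9 and 7.0 months.

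These are upper bounds. Only actual participants are barred, and patients who start treatment during the six-month recruitment period are never barred.

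**The case against.** **Comparability.** Recruitment says that the post-survey procedure will be identical, and the note to Figure 1 says that both surveys use the same institutions. A similar spread of time in treatment is therefore plausible, and the pre/post contrast would then be much less biased. This stands as a mitigating point. It does not ensure balance: practitioners select patients, and the intervention adds a special outpatient clinic that may change the mix of treatment stages. Nor does it turn scores taken during treatment into initiation values.

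**BMI.** Weight at initiation is already collected, so the BMI part is largely recoverable. This stands, although the article does not name it as the outcome and the weight is recalled.

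**Exploratory status and condensed text.** The hypotheses are secondary and exploratory, which lowers the weight of the point. Hand-out timing might also be set in the written recruitment information given to practitioners. So the claim is only that the article states no window. The mismatch between hypothesis and outcome is in the article's own text and is not a detail left to a fuller document.

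**Stronger readings that the documents do not support.**

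- *The bias works against the intervention.* A reader might infer this from the bar on pre-survey participants, which removes some long-stay patients from the post-sample. Step 5 shows that this mechanism alone cannot produce a 2-month gap at mean treatment lengths of 4 or 6 months, and other influences could act either way.
- *The bias can be half the effect that the trial is powered for.* That sets a symptom-score bias against an effect size specified for DUI. The two are not comparable.

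**Conclusion.** The point holds as a mismatch between two exploratory hypotheses and their measures. As planned, EDE-Q, PHQ-9, GAD-7 and current BMI mix severity at initiation with change under treatment, and nothing stated in the article limits or adjusts for time in treatment. Any pre/post difference in that time would bias the severity contrast and the mediation claim.

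The direction is unknown. The size cannot be taken from the documents: 0.025 to 0.40 SD follows from assumed changes of 0.05 to 0.2 SD per month and assumed differences of 0.5 to 2 months. If time in treatment is alike in both samples, the contrast suffers much less, but the label *at treatment initiation* is still wrong for these scores.

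This point does not touch the primary comparison of DUI. The change is worth making because it is cheap and brings the analysis closer to the stated hypotheses.

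**What to change.** 1. **BMI.** Make BMI at treatment initiation, from the weight already asked in the interview, the BMI outcome for hypothesis 3 in place of current BMI. Cost: the weight is recalled and so carries recall error.
2. **EDE-Q, PHQ-9 and GAD-7.** Adjust for months from treatment start to questionnaire completion, in both the period comparison and the analysis of the path through DUI. Use the same start date that ends the DUI; DUI already requires it. The article does not say that the completion date is recorded, so confirm this or add the field. Cost: at most one date per participant, and an assumption about the shape of change over time. Report the distribution of this interval by period.
3. **Sensitivity analysis.** Repeat with both samples restricted to questionnaires completed early in treatment, within a window fixed in advance. Cost: a smaller sample and wider intervals.
4. **Wording.** Describe the questionnaire results as pathology and comorbidity during first treatment, not at initiation. Cost: none beyond the text.

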**Figure 2 Fig2:**
[figure not shown]
**Expected impact of the systemic intervention on the primary and secondary outcome parameters.**

### Handling of missing values

Participants who appear unavailable for the telephone interview will be regarded as withdrawal. Analyses will be performed on completers due to the exploratory approach of the study. Additionally, sensitivity analyses using imputed data (fully conditional specification [46]) will be conducted.

### Statistical analyses

In order to test the primary hypotheses regarding change vs. no change from pre to post assessment univariate multiple regression analysis with the dependent variables DUI and DUC as well as the independent variable period of assessment will be conducted. Additionally, recruitment setting will be included as random control variable whereas age and contact with the systematic intervention will be taken into account as a fixed control variable. Statistical significance will be taken two-sided p <0.05 throughout and regression coefficient with 95% confidence intervals (CI) will be used to express the uncertainty in the data.

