**Figure 1 Fig1:**
[figure not shown]
**Course of data collection.** Note. Recruitment for pre- and post-survey occurred within the same institutions offering evidence-based treatment for AN based on the German S3-Guidelines for EDs [35].

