#### Duration until first contact with healthcare system (DUC)

The duration until first contact (DUC) is conceptualized as the number of months between illness onset and the first contact with the healthcare system due to ED-related issues initiated either by the patient or the practitioner. Before starting an ED-specific treatment, patients often have several initial contacts with healthcare professionals or advice centers. The variable DUI can not take these contacts into account because it is defined as the duration until the initiation of a guideline-based treatment. The DUC is meant to improve the understanding of the processes preceding treatment initiation. The questionnaire lists different potential therapeutic settings for AN (inpatient, day-clinic, outpatient, ED-specific counselling) and assesses which of these have been consulted to get information and/or support concerning AN and, in each case, when the first contact took place.

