In spite of the huge demand for such evaluated interventions, some limitations to this study have to be mentioned: Since this project is a systemic public health intervention, the implementation of a Randomized Controlled Trial (RCT) is not feasible. Therefore, it is problematic to control confounding factors and make causal conclusions. However, this limitation can be attributed to the aims of the project, which leaves no option of implementing a RCT. Due to the complexity of the systemic intervention it is further not realizable to conduct a dismantling investigation. It is assumed that some parts of the intervention act unconsciously. Therefore an entire understanding of the underlying dependencies will not be possible. Moreover, it is decided to exclude male patients from participation - admittedly at the expense of generalization of the results. The reasons for this decision can be found in the low prevalence of AN in males. It has to be noted that there is a lack of standardized measures assessing DUI and DUC. This makes it necessary to develop a new measure for the purposes of the study. Additionally, the variables of interest mainly can only be assessed retrospectively. To counteract a possible distortion, self-reported data is reviewed in the telephone interview. In addition, it has to be considered that a prospective study would not be feasible due to the low prevalence of AN. There are some further limitations concerning the recruitment of the participants. There may be an adherence bias of the cooperating practitioners leading to different participation rates. There may be also a selection bias: Chronified patients with extremely low body weight may display a very long DUI but may be excluded due to their current physical status. The consequence may be an underestimation of the average DUI in the sample.

Since there hasn’t been a comparable intervention in the field of AN, some hypotheses have to stay exploratory. However, the effectiveness of public health interventions in general could be shown already (e.g. [31]). In the field of EDs the *psychenet* intervention and its evaluation will gain new knowledge about the DUI and factors influencing this period. Also, the successful implementation of a systemic intervention in this area will improve the networking of different health care professionals and facilitate patients’ flow into specialist care.

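### The primary model's only clustering term appears to be care type, not recruiting institution, so a change in which institutions recruit would load on the pre-post effect

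*Protocol article*

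**What the plan says.** The Statistical analyses section regresses DUI and DUC on period (pre or post). Age and contact with the intervention are fixed covariates, and "recruitment setting will be included as random control variable". No institution or practitioner term is named, and the section does not say what counts as a recruitment setting.

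Two other sections show how the word is used:

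- Recruitment explains the treatment settings as "i.e. inpatient wards, day clinics, outpatient departments and ED-specific counselling centers".
- The DUC section says that the questionnaire lists "different potential therapeutic settings for AN (inpatient, day-clinic, outpatient, ED-specific counselling".

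Both list the same four care types. The individual sites are called institutions. The note to Figure 1 says "Recruitment for pre- and post-survey occurred within the same institutions", and Recruitment gives their number: "A total of eleven clinics, nineteen outpatient departments and four counselling centers are asked to support the project". That is 11 + 19 + 4 = 34 sites asked; the number that recruit is not given. No section fixes how many patients each institution contributes to either survey. The Discussion adds: "There may be an adherence bias of the cooperating practitioners leading to different participation rates".

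**The concern.** Practitioners at individual institutions select patients, obtain consent and return the forms, so recruitment can drift at that level. Institutions of the same care type may see patients with different typical DUI because of referral routes, age range or waiting times. If one outpatient department supplies many patients before the intervention and few after it, and another does the reverse, mean DUI can change although no patient reached treatment sooner. A care-type term cannot absorb this, because both departments belong to the same type.

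At stake is the primary conclusion. The study has no concurrent control group, so everything rests on the period coefficient and its 95% interval. An omitted institution effect would displace that coefficient at random and leave its standard error too small.

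**Working it through.** **The plan's own figure.** Inputs from Sample size/power calculation: standardised effect 0.4, two-sided 5%, power 80%, 100 per survey. Then n = 2(1.960 + 0.842)²/0.4² = 98.1, or 99 per group (99.1 with the t distribution). Power at 100 is 80.7% (80.4% with t). The figure reproduces as an ordinary comparison of two independent samples. The implied SD is 4.8/0.4 = 12 months.

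**What drives the error.** Take one care type, 100 patients per survey, and institution *i* contributing c0 patients before and c1 after. In units of the total variance, the true variance of the period difference is

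V = ICC × S/100² + (1 − ICC) × 2/100, with S = Σ(c1 − c0)².

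A model without an institution term works with about 2/100 = 0.02. Its type I error is therefore about 2Φ(−1.96 × √(0.02/V)).

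**Stable mix.** If recruiting shares stay the same and counts vary only by chance, S is about 100 + 100 = 200. Then V = ICC × 0.02 + (1 − ICC) × 0.02 = 0.02, and the error is 5.0% at every ICC. With exactly matched counts S = 0. At ICC 0.05, V = 0.019 and the error is 4.4%, slightly conservative.

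**Changed mix (assumed).** Overlap is the sum over institutions of the smaller of the two counts, divided by 100.

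- Pattern A: seven institutions gain 7 patients each and seven lose 7 each. Overlap is (100 − 49)/100 = 51%, and S = 14 × 49 = 686.
- Pattern B: seven gain 10 each and seven lose 10 each. Overlap is (100 − 70)/100 = 30%, and S = 14 × 100 = 1,400.

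| Assumed ICC | V, pattern A | Type I error | V, pattern B | Type I error |
|---|---|---|---|---|
| 0.05 | 0.0224 | 6.4% | 0.0260 | 8.6% |
| 0.10 | 0.0249 | 7.9% | 0.0320 | 12.1% |
| 0.15 | 0.0273 | 9.3% | 0.0380 | 15.5% |

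With the 12-month SD, the random displacement of the period effect has SD 12 × √(ICC × S/10,000). That is 0.7 months for pattern A at ICC 0.05 and 1.7 months for pattern B at ICC 0.15, against the 4.8 months sought. The model would report a standard error of 12 × √0.02 = 1.70 months, where the true one is 1.80 and 2.34 months respectively.

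**Simulation.** With 34 institutions (11, 19 and 4 by type), 100 patients per survey and the institution variance estimated by REML, the care-type-only model rejected a true null in the following shares of runs (ICC 0.05, 0.10, 0.15):

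- stable mix: about 5%
- 51% overlap: 6.5%, 8.6%, 9.6%
- 33% overlap: 8.5%, 12.1%, 15.3%

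With the institution random intercept the rate was 4.3% to 6.4%.

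**Milder turnover.** A separate calculation over random recruiting patterns gave, at ICC 0.05 and 0.10:

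- half of the recruiting weight redrawn: 5.4% and 5.7%
- about one third of institutions active in one survey only: 5.8% and 6.6%
- all shares redrawn: 6.5% and 8.0%
- all shares redrawn and concentrated in few institutions: 8.4% and 11.9%

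**The case against.** **The term may mean institution.** The model section does not define it, the study cooperates with sites and not with abstract care types, and declaring the factor random suits many sites better than four categories. This stands as a caveat: the care-type reading is well supported by usage, but it is inferred. The two readings give different primary models, so the wording needs settling either way.

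**The mix may not change.** The same institutions recruit twice, the post-survey procedure is to be identical, and practitioners are phoned to keep up adherence. The Discussion's remark on participation rates concerns differences between practitioners, not change over time, and constant differences do not bias the period effect. This stands, and it makes the harm conditional. But the plan neither fixes numbers per institution nor rules out a shift between two surveys that lie a year apart.

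**The remedy is imperfect.** One further simulation with estimated variance gave up to 7.2% for the institution model at ICC 0.05, against 7.9% without the term. The institution term does not guarantee 5% in every pattern.

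**Stronger readings that the article does not support.**

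- A reader might infer that the false-positive rate doubles. That needs an ICC of roughly 0.10 to 0.15 together with heavy turnover, and the article states neither.
- A reader might fault the random care-type factor because a variance over three or four levels is estimated as zero in 16% to 20% of samples at ICC 0.05. With 34 institutions the share is about 20% at the same ICC, so this does not separate the two models.
- A reader might call the sample size wrong. It reproduces, and because institutions are crossed with period, no standard cluster inflation follows.

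**Conclusion.** The concern holds in conditional form. On the article's own usage, the primary model adjusts for about four care types and leaves out the level at which patients are recruited. With a stable recruiting mix this does no harm, and the type I error is about 5%. Under assumed ICCs of 0.05 to 0.15 it is about 6.5% to 10% with about half overlap and about 8.5% to 15% with about one-third overlap, and the interval is correspondingly too narrow. Milder turnover gives 5.4% to 6.6% at ICC 0.05 to 0.10.

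These figures rest on an assumed ICC, assumed turnover, 34 active institutions in the simulations (34 is the number asked) and the care-type reading of the undefined term. The direction and the remedy do not depend on the exact values. It is a change worth making to the primary analysis, not evidence that its result would be wrong.

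**What to change.** In Statistical analyses, replace the random recruitment-setting term by a random intercept for recruiting institution, with care type (inpatient, day clinic, outpatient, counselling) as a fixed factor, for both DUI and DUC. If setting was meant as institution, say so and add care type as a fixed factor.

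Add a sensitivity analysis limited to institutions that recruited in both surveys, and report recruitment by institution and survey so that readers can judge the turnover. The sample size statement needs no change on this account.

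The cost is analysis wording. Institution should be known for every patient, because the cooperating practitioners return the forms. If the mix stays stable, little or nothing is lost. If it shifts, the interval becomes somewhat wider and power falls accordingly, which reflects the uncertainty actually present.

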#### Control variables

The questionnaire includes sociodemographic and control variables, such as age, gender, marital status, educational level, migration background, housing situation and occupational activity. At post assessment, patients are asked to indicate any contact with parts of the systemic interventions from *psychenet*. In case of positive response, further questions clarify which of the ED-specific interventions were recognized and if treatment initiation is subjectively eased by these interventions.

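### The regression that tests the pre/post change in DUI and DUC adjusts for reported contact with the intervention, which only the post sample is asked about, so its period coefficient is not the hypothesised post-versus-pre difference

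*Protocol article*

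**What the plan says.** The first hypothesis (Study hypotheses) is a contrast between the two samples: "The systemic intervention decreases the DUI in the post-group compared to the pre-group". The second says the same for DUC.

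Under Statistical analyses, these are tested by regressing DUI and DUC on period: "the independent variable period of assessment will be conducted". The next sentence gives the remaining terms: "recruitment setting will be included as random control variable", while "age and contact with the systematic intervention will be taken into account as a fixed control variable". No version of this model without contact is described.

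The Control variables section places the contact question in the second survey only: "At post assessment, patients are asked to indicate any contact with parts of the systemic interventions". The Recruitment section gives the order of events, "Between the two points of data collection the systemic intervention takes place", and bars pre-survey participants from the post-survey, so the samples do not overlap.

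The Discussion adds: "It is assumed that some parts of the intervention act unconsciously".

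**The concern.** A control variable should be something that differs between the periods for reasons other than the intervention. Contact is not of that kind. It comes about because the intervention took place, and it is one of the routes by which the intervention could shorten DUI. It also cannot serve as a balancing variable, because one of the two samples is never asked.

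Hypotheses 1 and 2 are read off the period coefficient. With contact held fixed, that coefficient describes only the change seen in patients who noticed nothing. Any benefit in patients who did notice the programme moves to the contact coefficient. Because contact can be positive only in the post sample, it is also correlated with period, and the standard error rises. The trial could therefore miss, or understate, a reduction of the size it was planned to detect.

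**Working it through.** **Inputs from the Sample size section.** 100 per sample, two-sided 5%, power 80%, target reduction 4.8 months, effect size 0.4, mean DUI 19 months. The SD is not stated; it is implied as 4.8 / 0.4 = 12 months.

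**Assumptions, not in the article.** q is the share of post patients reporting contact, taken as 30, 50 and 70%. m is the fraction of the average effect that runs through reported contact, taken as 0, one half and 1. Contact is coded 0 for every pre patient. Age and the random setting term are left out.

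**1. The article's own figure.** n per sample = 2 × (1.96 + 0.84)² × 12² / 4.8² = 98.1, so 99 by the normal approximation. The t-test solution is 99.08, so 100. Power at 100 per sample is 80.4% by t-test. The stated size is reproduced, and it belongs to a two-sample comparison without a contact term. The standard error is 12 × √(1/100 + 1/100) = 1.70 months.

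**2. What period estimates once contact is in the model.** There are three cells: pre, post without contact and post with contact. The model has an intercept, a period term and a contact term, so it fits the three cell means exactly. Hence

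- period coefficient = mean(post, no contact) − mean(pre)
- contact coefficient = mean(post, contact) − mean(post, no contact)

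**3. Expected value.** With a total difference of −4.8 months, the period coefficient has expectation −4.8 × (1 − m): −4.8 for m = 0, −2.4 for m = ½ and 0 for m = 1.

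**4. Precision.** SE = 12 × √(1/100 + 1/(100(1 − q))). Relative to the unadjusted comparison, the variance is inflated by (2 − q)/(2 − 2q).

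| q | SE (months) | Variance inflation | Power, m = 0 | Power, m = ½ | Rejection rate, m = 1 |
|---|---|---|---|---|---|
| no contact term | 1.70 | 1 | 80% | 80% | 80% |
| 30% | 1.87 | 1.21 | 72% | 25% | 5% |
| 50% | 2.08 | 1.50 | 63% | 21% | 5% |
| 70% | 2.50 | 2.17 | 48% | 16% | 5% |

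Example, q = 50%: SE = 12 × √(0.01 + 0.02) = 2.08. For m = 0 the ratio is 4.8/2.08 = 2.31, giving 63%. For m = ½ it is 2.4/2.08 = 1.15, giving 21%.

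The 80% in the first row is nominal for m = ½ and m = 1, where the effect differs between post patients and adds some spread to the post sample.

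**5. Simulation check.** With 2,000 simulated trials at q = 50%, the mean period coefficients were −4.82, −2.40 and −0.06 for m = 0, ½ and 1. Without the contact term they were about −4.8 in all three cases.

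**6. The other possible coding.** If contact were left missing for pre participants, a completer fit would keep only post patients. Period would then be constant and could not be estimated.

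**The case against.** **The sentence may describe a further analysis.** The test is first defined on period alone, the covariate sentence opens with an additive word, and the sample size matches an unadjusted comparison. This is possible but strained. The sentence assigns setting a random role and age and contact a fixed role, which is how terms of one model are listed. If a separate model was meant, the article should say so.

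**The effect is not necessarily lost.** A reader might infer that the adjusted period coefficient removes the intervention effect altogether. The documents do not support that. It would require the whole effect to run through contact that patients report, whereas the article assumes that some parts work unnoticed, and the professional network acts through practitioners. The m = 1 column is also demanding: at q = 30%, contacted patients would have to gain 4.8/0.3 = 16 months, or 84% of the 19-month mean. It marks a limit and is not a forecast.

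**The signal moves to another coefficient.** In that same extreme case, the contact coefficient would be significant with about 100, 98 and 74% power at q = 30, 50 and 70%. This is true, but hypotheses 1 and 2 concern period. The contact coefficient compares patients who did and did not notice the programme, and that comparison is open to self-selection.

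**Imputation and complete-case loss are conjecture.** A reader might infer that the planned imputation would create contact values for the pre sample, or that the pre sample would drop out. The article states neither. Both depend on a coding it does not give, and step 6 is conditional for that reason.

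**Removing contact does not give a causal effect.** This stands. The Discussion concedes that confounding is hard to control in this design. The wider research network was also active from 2011, before the pre-survey, so zero exposure in the pre sample is itself an assumption.

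**Conclusion.** The point holds. As most naturally read, the model for hypotheses 1 and 2 adjusts for a post-exposure variable that is recorded in one sample only. Its period coefficient is then the difference between post patients without reported contact and the pre sample, which is not the contrast hypothesised.

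The direction of the loss is clear: attenuation to the extent that the effect runs through reported contact, plus reduced precision at any contact share above zero. Its amount is not known. Over contact shares of 30 to 70%, the planned 80% power becomes 72 to 48% if contact plays no part in the effect, and about 25 to 16% if it carries half. The figure of about 5% is the limiting case. These values rest on an SD of 12 months, contact coded 0 in the pre sample, and assumed values for q and m. They leave aside selection: post patients who noticed nothing may differ from pre patients in other ways, which could bias the coefficient in either direction.

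The sample size calculation itself is not in dispute.

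**What to change.** Remove contact with the intervention from the primary DUI and DUC models, keeping period, age and the random setting term. Period then estimates the total pre/post difference, which is the comparison the study was sized for, subject to the limits of an uncontrolled design that the Discussion already states.

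Use contact only in an analysis labelled exploratory: a descriptive comparison within the post sample, or a mediation analysis with its assumptions stated. State that contact is not to be imputed for pre participants.

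The cost is one changed sentence under Statistical analyses and a short addition for the exploratory use. No new data are needed and the sample size is unchanged.
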